**Objective:**

We will compare the feasibility of MHB versus an education control (health enhancement program [HEP]) in 50 older adults (aged ≥60 y) with subjective cognitive decline and AD/ADRD risk factors. In an NIH stage 1B randomized controlled trial (RCT), we will evaluate feasibility benchmarks, improvements in cognitive and lifestyle outcomes, and engagement of hypothesized mechanisms.

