**Methods:**

We are recruiting through clinics, flyers, web-based research platforms, and community partnerships. Participants are randomized to MHB or the HEP, both delivered in telehealth groups over 8 weeks. MHB participants learn behavior modification and mindfulness skills to achieve individualized lifestyle goals. HEP participants receive lifestyle education and group support. Assessments are repeated after the intervention and at a 6-month follow-up. Our primary outcomes are feasibility, acceptability, appropriateness, credibility, satisfaction, and fidelity benchmarks. The secondary outcomes are cognitive function and lifestyle (physical activity, sleep, nutrition, alcohol and tobacco use, and mental and social activity) behaviors. Data analyses will include the proportion of MHB and HEP participants who meet each benchmark (primary outcome) and paired samples 2-tailed *t* tests, Cohen *d* effect sizes, and the minimal clinically important difference for each measure (secondary outcomes).

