#### Exploratory Assessments

##### Multiday Boston Remote Assessment for Neurocognitive Health

We are exploring the feasibility of integrating daily mobile cognitive functioning assessments via the Boston Remote Assessment for Neurocognitive Health (BRANCH) platform [160,187,188]. The multiday paradigm using BRANCH can be self-administered without researcher supervision using any web-enabled device (mobile phone, tablet device, or computer). Similar to RBANS assessments, we provide an iPad for participants who do not own a web-enabled device to complete the multiday BRANCH tests. Participants complete 1 BRANCH test per day for 7 days during the 3 main assessment periods; they complete a unique version at each time point (before the intervention, after the intervention, and the 6-month follow-up). Participants complete a brief sequence of three visual associative memory tasks involving everyday objects: (1) Digit-Signs Test (correct number of street sign–number pairings identified), (2) Groceries Prices Test (correct number of grocery-price pairings identified), and (3) Face-Name Test (average of correct responses from 2 face-name pairings: first letter name recall and full name recall). Multiday learning curves to capture the speed and learning of BRANCH stimuli will be computed for each task [160]. Participants are instructed to take the multiday BRANCH tests in a quiet, distraction-free environment. Participants indicate a preferred time to complete the assessment once per day. They receive automated and secure SMS text messages or email reminders with a link to access the test. The administration of the multiday BRANCH tests takes approximately 12 minutes per day. The multiday BRANCH tests have demonstrated strong feasibility, reliability, validity, and sensitivity to subtle changes in learning and memory in preclinical AD/ADRD [160,189].

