#### HEP Control

The HEP is a time- and attention-matched education control [68,69]. The HEP has been used in similar RCTs, including those involving older adults with SCD [74,81,83,92,197-201]. This active control accounts for the effect of time spent as well as feedback and support from group members and the study clinician. Participants receive lifestyle education consistent with public health recommendations and standards for health promotion (eg, physical activity, sleep, and the Mediterranean diet; Textbox 2). Participants do not learn the mindfulness or behavior modification skills unique to MHB. To control for the time and attention devoted to MHB skills, HEP participants are instructed to journal for 5 to 10 minutes per day. HEP participants wear the Garmin Vivosmart 5 but do not monitor steps and sleep or set goals (ie, these features are disabled in the Garmin Connect app).

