#### Exploratory Analyses

Consistent with the Science of Behavior Change framework [189], we will test preliminary improvements and explore mechanisms to guide intervention refinements before efficacy testing. For each measure, we will report descriptive statistics, paired samples 2-tailed *t* tests, and Cohen *d* effect sizes (small=0.2, medium=0.5, and large=0.8) [204] with 95% CIs and minimal clinically important difference where available. We will analyze the MHB and HEP groups separately. We will explore associations between hypothesized mechanisms and outcomes to gauge the evidence of engagement in the targets of the MHB intervention. Finally, we will examine adherence and person-specific patterns of intensive longitudinal data (Garmin Vivosmart 5, multiday BRANCH tests, and daily surveys) during the RCT.

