## Discussion

### Summary

SCD represents a critical opportunity for early intervention to modify risk factors for AD/ADRD. MHB addresses this gap by offering a novel group mindfulness-based lifestyle program tailored to older adults with SCD. Single-arm open pilot studies (NIH stage 1A) have demonstrated the feasibility and acceptability of MHB, indicating its potential to bypass challenges to lifestyle behavior modification and improve cognitive outcomes among older adults. These preliminary studies also revealed barriers to participation that must be addressed during the design and execution of the first RCT of MHB before conducting fully powered trials or implementing the program in clinical care.

The primary aim of this feasibility RCT is to establish the feasibility, acceptability, appropriateness, credibility, satisfaction, and fidelity of the MHB intervention compared to the HEP active control (NIH stage 1B). Our secondary aim is to explore preliminary signals of improvement in outcomes and hypothesized mechanisms (Table 1 and Figure 3). Testing these aims and our ability to randomize participants to MHB versus the HEP will serve as a “dress rehearsal” for a subsequent efficacy RCT. In addition, this RCT will provide valuable insights into the feasibility of integrating multiple digital health technologies into a lifestyle trial for older adults with SCD. If feasible, the novel integration of passive activity sensors, repeated mobile cognitive assessments, and daily surveys offer a comprehensive framework for monitoring adherence and understanding individual responses to lifestyle interventions and the mechanisms of action. This is notable because the pathways by which lifestyle interventions may improve cognitive outcomes and prevent AD/ADRD among older adults with SCD are poorly understood.

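### Cognitive, lifestyle and mechanism outcomes are tested only before-after within each arm, so the randomized MHB–HEP contrast plays no part in outcome inference

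*Protocol article*

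**What the plan says.** Under Exploratory Analyses the protocol article states its purpose as "we will test preliminary improvements and explore mechanisms to guide intervention refinements before efficacy testing". The t tests it lists compare before with after: the list of methods opens with "we will report descriptive statistics, paired samples 2-tailed", and Cohen d with 95% CI and, where one exists, the minimal clinically important difference complete it. The same paragraph adds: "We will analyze the MHB and HEP groups separately".

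The Abstract (Methods) names the same paired tests for what it ranks as secondary: "The secondary outcomes are cognitive function and lifestyle" behaviors.

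The reason for the control arm is given under HEP Control: "This active control accounts for the effect of time spent as well as feedback and support from group members and the study clinician". The Discussion (Summary) describes the trial as a rehearsal for an efficacy RCT, and the Conclusions say that the later trial will test superiority of MHB over HEP.

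Two statements limit the weight of the point. The Power Analysis section says that the trial concerns feasibility benchmarks and not efficacy. Primary Analyses reports those benchmarks by arm and rests the decision to proceed on them.

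**The concern.** An active control removes the effect of time, attention and group support only when its change is subtracted from the change in the intervention arm. Two separate paired tests do not subtract anything. Each asks whether its own arm changed, and in a three-visit study of volunteers with current complaints an arm can change for reasons unrelated to the mindfulness and behavior-change content.

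The document itself shows several such reasons:
- expectancy and group support, present in both arms;
- general time trends;
- repeated cognitive testing. Alternate RBANS forms reduce practice effects but do not remove them. For BRANCH, "they complete a unique version at each time point", so version is tied to visit and any difference in difficulty looks like change;
- some regression to the mean, since people are selected for low activity and current cognitive complaints.

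At stake is the secondary aim: preliminary improvement and engagement of mechanisms. The quantity that stage 2 must be planned on is MHB minus HEP. The single-arm pilots already supplied within-arm improvements, so a paired test in the MHB arm adds evidence of the same kind and leaves the gain from randomization unused.

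**Working it through.** **The plan's own figure.** The only power statement concerns the benchmarks (more than 80% with 50 participants, 10 independent criteria, true rate 82%). It reproduces: P(X ≥ 35 | n=50, p=0.82) = 0.988, and 0.988^10 = 0.886. It says nothing about the paired tests, for which no operating characteristic is given.

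**Inputs for the illustration.**
- From the document: 50 participants, allocated 1:1, so about 25 per arm; two-tailed paired tests; 95% CIs.
- Assumed: two-sided alpha 0.05, no dropout, no program effect, and the same true change in both arms. That shared change is d = 0.2 or 0.3 in units of the outcome SD, with before-after correlation r = 0.5, 0.7 or 0.8. The document gives neither a practice or time effect nor a correlation, hence the range.

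**Within-arm test.** The standardized change is dz = d / √(2(1−r)). The noncentrality is dz × √25, on 24 df, with critical value 2.064.

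| d | r | dz | noncentrality | P(paired test significant) |
|---|---|---|---|---|
| 0.2 | 0.5 | 0.200 | 1.00 | 16% |
| 0.2 | 0.7 | 0.258 | 1.29 | 24% |
| 0.2 | 0.8 | 0.316 | 1.58 | 33% |
| 0.3 | 0.5 | 0.300 | 1.50 | 30% |
| 0.3 | 0.7 | 0.387 | 1.94 | 46% |
| 0.3 | 0.8 | 0.474 | 2.37 | 62% |

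**Between-arm test on the same data.** The shared change cancels, so the rejection rate is 5%. A simulation of 20,000 trials gave 5.1% and 5.0% at shared standardized changes (dz) of 0.3 and 0.5.

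**Significant in MHB but not in HEP, with no program effect.** With independent arms this has probability p(1−p). At p = 0.161 it is 0.161 × 0.839 = 0.135; at p = 0.46 it is 0.46 × 0.54 = 0.25. Over the table it runs from about 14% to 25%.

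**What the contrast would deliver.** The 95% half-width for a standardized between-arm difference with 25 per arm is 1.96 × √(2/25) = 0.55 SD. Adjusting for baseline multiplies this by √(1−r²); at r = 0.7 that is 0.55 × √0.51 = 0.40 SD. With the t quantile on 48 df in place of 1.96, the unadjusted figure is 0.57.

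**The case against.** The strongest reply is that this is a stage 1B feasibility trial. The tests are labelled exploratory, efficacy testing is disclaimed, superiority is left to stage 2, and the decision to proceed rests on benchmarks alone. That stands, and it sets the severity at moderate. It does not remove the point: a study that disclaims efficacy testing has as little use for within-arm t tests as for between-arm ones, and the Abstract lists cognition and lifestyle as secondary outcomes.

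Several stronger readings are tempting but unsupported:

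- *The control arm is never used.* HEP has its own benchmarks, and its changes, d values and intervals will be reported beside those of MHB. What is missing is the formal difference and its uncertainty.
- *The authors will attribute within-arm change to MHB, or compare significance between arms.* No section says so. The risk comes from the chosen analysis and is not a stated intention.
- *Within-arm d will overstate the effect.* It can, but time trends and version difficulty can act in either direction.
- *Practice effects drive the problem.* They concern only the performance tests (RBANS and the exploratory BRANCH), and both use alternate material, which also limits relearning of items. Most measures are self-report or wearable.
- *Regression to the mean in step count is large.* Selection uses self-reported activity at screening, whereas the baseline is a separate, later Garmin measurement. Much of the regression should occur before that baseline.
- *The benchmarks also need a between-arm difference.* The Abstract does say "We will compare the feasibility of MHB versus an education control", and the Summary says "compared to the HEP active control". But the thresholds apply to each program, and a difference in proportions would change no decision.

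An analysis plan that is not shown could contain the contrast. The published sentence, however, does not leave the matter open; it fixes separate analysis.

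**Conclusion.** The point holds for cognitive, lifestyle and mechanism outcomes. The stated analysis makes no inferential use of randomization, so it cannot separate a program effect from change that both arms share. How often this misleads depends on assumptions: with a shared change of d = 0.2 to 0.3 and r = 0.5 to 0.8, the paired test is significant in 16% to 62% of trials with no program effect, against 5% for the contrast. A smaller shared change or a lower correlation would bring the figure nearer 5%. The existence of the problem does not depend on these values.

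Severity is moderate. The primary feasibility conclusions and the go/no-go decision are untouched. What is affected is how the secondary results can be read and what stage 2 is planned on. A reader should not infer that the trial's main conclusions are at risk.

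**What to change.** Replace the sentence on separate analysis. For each cognitive, lifestyle and mechanism outcome, estimate the MHB–HEP difference at post-intervention and at 6 months, adjusted for the baseline value, by ANCOVA or by a mixed model over both follow-ups. Report the adjusted difference and a standardized effect with 95% CI, labelled as estimation and without significance claims. Keep within-arm means, changes and d values as description only, and drop the reading of paired p values as tests of improvement. Per-arm reporting of the benchmarks can stay.

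The cost is a change of wording and a few lines of R. The data are already planned to be collected, and no extra visits or participants are needed. The downside is imprecision: half-widths of about 0.55 SD unadjusted, or 0.40 SD adjusted at r = 0.7, with 25 per arm. They will be wider with dropout, and correlation within the telehealth groups may widen them further. The contrast will therefore add little precision for planning, but it will show the uncertainty of the quantity that stage 2 needs.

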## Results

### Overview

This study was funded by a National Institute on Aging Mentored Patient-Oriented Research Career Development Award (K23; 1 K23 AG075257-01; September 2022). The study was approved by the IRB in October 2023. We began recruitment in January 2024. As of June 1, 2024, a total of 225 individuals had inquired about the study via self-referral or referral from a clinician or community partner. We made initial contact and conducted screenings with 213 (94.7%) of the 225 individuals; 25.6% (40/156) met the eligibility criteria. Of the 40 eligible participants, 21 (52.5%) were enrolled in 2 group cohorts, 17 (42.5%) were on hold for future group cohorts, and 2 (5%) withdrew before enrollment. Primary reasons for ineligibility included low AD/ADRD risk (CAIDE score <6; 54/116, 46.6%), active lifestyle (>5000 average steps per day and ≥30 minutes of exercise per day; 26/116, 22.4%), no self-reported SCD (18/116, 15.5%), age <60 years (16/116, 13.8%), regular mindfulness practice (8/116, 6.9%), and clinically significant cognitive impairment (Telephone Interview for Cognitive Status score <31 out of a maximum possible 41 points; 5/116, 4.3%).

All 21 enrolled participants were randomized to MHB (n=11, 52%) or the HEP (n=10, 48%) across 2 group cohorts (cohort 1: n=9, 43%; cohort 2: n=12, 57%). All participants completed before the intervention assessments. No participants have dropped out after enrollment. All participants in our first cohort completed ≥6 out of 8 sessions of either MHB or the HEP (including minimal makeup sessions) and after the intervention assessments (9/9, 100%). One participant requested to skip the HEP session on substance use due to a traumatic family history. The intervention for our second cohort (12/21, 57%) is ongoing (5 out of 8 sessions completed; 100% attendance with minimal makeup sessions). Across both cohorts, adherence rates are high for the Garmin Vivosmart 5 (128/147, 87.1% total weeks) and daily surveys (105/122, 86.1% total weeks). We plan to complete enrollment by December 2024 and data analyses by December 2025.

### Demographics

Sample characteristics for enrolled cohorts 1 and 2 are presented in Table 3.

**Table 3 table3:** Demographics of enrolled and scheduled My Healthy Brain study participants (n=21).

Characteristics		Values
Age (y), mean (SD; range)		72 (7.71; 60-88)
**Sex, n (%)**		
	Female	16 (76)
	Male	5 (24)
	Chose not to answer	0 (0)
**Gender, n (%)**		
	Women	16 (76)
	Men	5 (24)
	Nonbinary	0 (0)
	Chose not to answer	0 (0)
**Ethnicity, n (%)**		
	Hispanic or Latinx	1 (5)
	Not Hispanic or Latinx	19 (91)
	Chose not to answer	1 (5)
**Race, n (%)**		
	Asian or Asian American	1 (5)
	Black or African American	1 (5)
	White	17 (81)
	Multiracial	0 (0)
	Chose not to answer	2 (10)
**Marital status, n (%)**		
	Single, never married	2 (11)
	Married	9 (43)
	Living with significant other	0 (0)
	Separated or divorced	5 (24)
	Widowed	5 (24)
	Chose not to answer	0 (0)
**Living status, n (%)**		
	Live alone	7 (33)
	Live alone with spouse or partner	9 (43)
	Live alone with 1 other friend or roommate	2 (10)
	Live with caregiver	0 (0)
	Live with group (private residence)	2 (10)
	Live in a group home	1 (5)
	Other	0 (0)
	Chose not to answer	0 (0)
**Education, n (%)**		
	Completed high school or GED^a^ (12 y)	1 (5)
	Some college or associate’s degree (<16 y)	2 (10)
	Completed 4 years of college (16 y)	8 (38)
	Graduate or professional degree (>16 y)	10 (48)
	Chose not to answer	0 (0)
**Employment status, n (%)**		
	Employed full time	5 (24)
	Employed part time	4 (19)
	Retired	12 (57)
	Other	0 (0)
	Chose not to answer	0 (0)
**Income (US $), n (%)**		
	<10,000	1 (5)
	10,000 to <15,000	0 (0)
	15,000 to <20,000	0 (0)
	20,000 to <25,000	3 (14)
	25,000 to <35,000	1 (5)
	35,000 to <50,000	3 (14)
	50,000 to <75,000	6 (29)
	75,000 to <100,000	3 (14)
	≥100,000	4 (19)
	Chose not to answer	0 (0)

^a^GED: General Educational Development.

## Discussion

### Summary

SCD represents a critical opportunity for early intervention to modify risk factors for AD/ADRD. MHB addresses this gap by offering a novel group mindfulness-based lifestyle program tailored to older adults with SCD. Single-arm open pilot studies (NIH stage 1A) have demonstrated the feasibility and acceptability of MHB, indicating its potential to bypass challenges to lifestyle behavior modification and improve cognitive outcomes among older adults. These preliminary studies also revealed barriers to participation that must be addressed during the design and execution of the first RCT of MHB before conducting fully powered trials or implementing the program in clinical care.

The primary aim of this feasibility RCT is to establish the feasibility, acceptability, appropriateness, credibility, satisfaction, and fidelity of the MHB intervention compared to the HEP active control (NIH stage 1B). Our secondary aim is to explore preliminary signals of improvement in outcomes and hypothesized mechanisms (Table 1 and Figure 3). Testing these aims and our ability to randomize participants to MHB versus the HEP will serve as a “dress rehearsal” for a subsequent efficacy RCT. In addition, this RCT will provide valuable insights into the feasibility of integrating multiple digital health technologies into a lifestyle trial for older adults with SCD. If feasible, the novel integration of passive activity sensors, repeated mobile cognitive assessments, and daily surveys offer a comprehensive framework for monitoring adherence and understanding individual responses to lifestyle interventions and the mechanisms of action. This is notable because the pathways by which lifestyle interventions may improve cognitive outcomes and prevent AD/ADRD among older adults with SCD are poorly understood.

We have made several changes to our study protocol (Multimedia Appendix 1) guided by our qualitative studies [67]. Using implementation science frameworks [205-207] and the socioecological model [208], the protocol changes and strategies aim to maximize RCT outcomes, increase sample diversity within our RCT, and reduce barriers to AD/ADRD prevention efforts [209-212]. Initial observations suggest that our protocol changes and strategies have been effective. We have observed a high volume of inquiries, indicating that our outreach efforts have been successful and that older adults are interested in participating in the study. Participant adherence to both programs is notably high, with positive engagement in the mindfulness and behavior change skills taught in MHB. Preliminary Garmin Vivosmart 5 and daily survey adherence data are also promising but must be confirmed upon study completion. Providing individualized support and devices at no cost has enabled us to include and retain older adults with limited technological access or proficiency [209,210,213]. To date, the enrolled participants predominantly represent White, well-educated women. In our next group cohorts, we will prioritize the inclusion of racial and ethnic minoritized older adults to address their underrepresentation in prevention RCTs and their increased risk of AD/ADRD [101,102]. We are conducting broader outreach, including both professional and community groups, to further increase awareness and diverse participation [214,215]. The feasibility RCT will provide initial information on our ability to engage older adult communities in AD/ADRD prevention research.

### Limitations

Despite the protocol improvements, several limitations remain and are outlined in the following subsections (additional limitations may arise during the execution of our trial).

#### Sample Diversity

While we have increased the diversity of our recruitment sources through community outreach, it is difficult to enroll racial and ethnic minoritized older adults. It takes time to build trust in community partnerships and address barriers to participation in clinical trials rooted in social determinants of health [216]. In addition, our interventions are currently only available in English, which greatly limits our ability to include many older adults in our community who speak Spanish or other languages. To address disparities in AD/ADRD prevention, future studies will incorporate principles of community-based participatory research and set benchmarks for enrolling minoritized older adults.

